## **5.2 Trial volunteers**

Adult volunteers aged at least 18 years, will be recruited into the study. Volunteers will be considered enrolled immediately following administration of the vaccine.

## **5.3 Definition of End of Trial**

The end of the trial is the date of the last assay conducted on the last sample collected.

## **5.4 Potential Risks for volunteers**

The potential risks are those associated with phlebotomy, vaccination and disease enhancement

### **Venepuncture**

#### **Adult Groups**

Localised bruising and discomfort can occur at the site of venepuncture. Infrequently fainting may occur. These will not be documented as AEs if they occur. The total volume of blood drawn over a 12 month period will be 105-687.5mL in the adult groups (blood volumes may vary slightly for volunteers at different investigator sites due to use of different volume vacutainers, following local Trust SOPs). The total volume of blood drawn over a 12 month period in the HIV group will be 1077.5mL. This should not compromise these otherwise healthy volunteers, as they would donate 470mL during a single blood donation for the National Blood transfusion Service over a 3-4 month period.

As of SA23 (protocol V18.0), participants will be permitted to donate blood to transfusion services from 3 months after the date of their final planned study vaccination. This replaces the previous instruction that volunteers should refrain from blood donation for the duration of their involvement in the trial. 3 months has been selected to provide adequate spacing between study visits and blood

donation in order to remain within the recommended limits for blood donation in the UK and to comply with the Joint United Kingdom (UK) Blood Transfusion and Tissue Transplantation Services Professional Advisory Committee requirement for a minimum period of 7 days between ChAdOx1 nCov-19 vaccination and blood donation (Joint United Kingdom (UK) Blood Transfusion and Tissue Transplantation Services Professional Advisory Committee: Change Notification UK National Blood Services No. 73 - 2020).

### **Allergic reactions**

Allergic reactions from mild to severe may occur in response to any constituent of a medicinal product's preparation. Anaphylaxis is extremely rare (about 1 in 1,000,000 vaccine doses) but can occur in response to any vaccine or medication.

### **Vaccination**

#### *Local reaction from IM vaccination*

The typical local reaction as a result of IM injection is temporary pain, tenderness, redness, and swelling at the site of the injection.

#### *Systemic reactions*

Constitutional influenza-like symptoms such as fatigue, headache, malaise, feverishness, and muscle aches can occur with any vaccination and last for approximately 2-3 days. In the phase 1 COV001 study, approximately 30-40% of participants not taking prophylactic paracetamol felt feverishness, or had chills, muscle ache, malaise, fatigue, or headache which they rated as moderate to severe. (See the investigator brochure for further details). Presyncopal and syncopal episodes may occur at the time of vaccination which rapidly resolve. As with many vaccines, temporary ascending paralysis (Guillain-Barré syndrome, GBS) or immune mediated reactions that can lead to organ damage may occur, but this should be extremely rare (1 in 100,000-1,000,000 vaccine doses).

Transient neutropenia, lymphopenia and thrombocytopenia has been described following immunization with other adenoviral-vectored vaccines, and is not perceived to be of clinical significance.

Control participants will receive one or two doses of a licensed MenACWY vaccine, the risks of which are described in these vaccines SmPC.

### **Disease Enhancement**

The risks of inducing disease enhancement and lung immunopathology in the event of COVID-19 disease following ChAdOx1 nCoV-19 vaccination are unknown as described above. Two NHP challenge studies have shown no evidence of disease enhancement from immunisation with ChAdOx1 nCoV-19 or inactivated SARS-CoV-2 virus, but caution should be taken when interpreting these negative findings. All pre-clinical data from challenge studies using ChAdOx1 nCoV-19 and other vaccine candidates (when available) will inform decisions on risk/benefit to participants receiving the IMP. Any safety signals associated with disease enhancement potentially observed in COV001 will also inform these decisions.

### **Emerging Thrombosis with Thrombocytopenia Association with vaccination**

The MHRA and JCVI issued updated guidance regarding the use of ChAdOx1 nCoV-19 on 7th April 2021, following a review of extremely rare reports of cerebral venous sinus thrombosis (and thrombosis of other major veins) with concurrent thrombocytopenia that have occurred after vaccination in the national rollout programme. This recommends that currently, in the UK setting, alternative vaccinations against COVID-19 should be preferentially offered to individuals aged 29 and under.

Prior to any further participant receiving ChAdOx1 nCoV-19 in this trial, they will be provided with up-to-date information from regulators on this finding via the updated participant information sheet. They will also be provided with other relevant documentation from regulators and/or public health authorities related to this association and possible risks of vaccination that is also being provided in vaccination centres. Participants will be advised to be aware of possible signs and symptoms of blood clots and to have a low threshold to contact trial teams if experiencing these or other symptoms. Following this recommendation, no further ChAdOx1 nCoV-19 prime vaccination doses will be administered to participants aged 29 and under within this trial. This age restriction recommendation does not apply to booster vaccinations which may therefore continue to be administered within the trial to participants of any age.

## 5.5 Known Potential Benefits

Volunteers enrolled into the control groups will receive 1 or 2 doses of MenACWY, a licensed vaccine that has been administered to teenagers in the UK routine schedule since 2015 and is used as a travel vaccine for high risk areas. The majority of participants in this study will not have had this vaccine previously, and therefore will gain the benefit of protection against group A, C, W and Y meningococcus. Those participants who have previously had MenACWY vaccines will have their immunity against these organisms boosted. Recipients of ChAdOx1 nCoV-19 do not have any guaranteed benefit, however it is hoped that the information gained from this study will contribute to the development of a safe and effective vaccine against COVID-19.

## 6 RECRUITMENT AND WITHDRAWAL OF TRIAL VOLUNTEERS

### 6.1 Identification of Trial Volunteers

Volunteers will be recruited by use of an advertisement +/- registration form formally approved by the ethics committee(s) and distributed or posted in the following places:

- In public places, including buses and trains, with the agreement of the owner / proprietor.
- In newspapers or other literature for circulation.
- On radio via announcements.
- On a website or social media site operated by our group or with the agreement of the owner or operator (including on-line recruitment through our website).
- By e-mail distribution to a group or list only with the express agreement of the network administrator or with equivalent authorisation.
- By email distribution to individuals who have already expressed an interest in taking part in any clinical trial at the Oxford Vaccine Centre and at trial sites.
- On stalls or stands at exhibitions or fairs.
- Via presentations (e.g. presentations at lectures or invited seminars).
- Direct mail-out: This will involve obtaining names and addresses of adults via the most recent Electoral Roll. The contact details of individuals who have indicated that they do not wish to

receive postal mail-shots would be removed prior to the investigators being given this information. The company providing this service is registered under the General Data Protection Regulation 2016/679. Investigators would not be given dates of birth or ages of individuals but the list supplied would only contain names of those aged  $\geq 18$  years (as per the inclusion criteria).

- Direct mail-out using National Health Service databases: These include the National Health Applications and Infrastructure Services (NHAIS) via a NHAIS data extract or equivalent. Initial contact to potential participants will not be made by the study team. Instead study invitation material will be sent out on our behalf by an external company, CFH Docmail Ltd, in order to preserve the confidentiality of potential participants. CFH Docmail Ltd is accredited as having exceeded standards under the NHS Digital Data Security and Protection Toolkit (ODS ID – 8HN70).
- Oxford Vaccine Centre databases and study site databases: We may contact individuals from databases of groups within the CCVTM (including the Oxford Vaccine Centre database) and other study sites of previous trial participants who have expressed an interest in receiving information about all future studies for which they may be eligible.
- Using local GP practices or Trusts as Participant Identification Centres (PICs)

Recruitment of those with likely higher exposure to SARS-CoV-2 will be prioritised, in order to increase the likelihood of obtaining efficacy endpoints in the context of a waning epidemic. These priority groups will mainly consist of, but are not limited to, COVID-19 patient facing frontline healthcare workers (e.g. those working in ICU, A&E, COVID-19 wards, Paramedics, Care Homes, GP COVID-19 hubs, dentists, COVID-19 testing centres), non-healthcare staff working in COVID-19 clinical areas (e.g. hospital porters, receptionists, cleaners, other hospital workers), and other public facing keyworkers with no access to personal protective equipment, amongst others.

## 6.2 Informed consent

Participants will personally sign and date the latest approved version of the Informed Consent form. A written version and verbal explanation of the Study Information leaflet and Informed Consent will be presented to the participant/parent/legal guardian of the participant detailing:

- the exact nature of the study

- what it will involve for the participant
- the implications and constraints of the protocol
- the known side effects and any risks involved in taking part
- sample handling – participants will be informed that anonymised samples taken during the course of the study may be shared with study collaborators.
- Individual results will not be shared with participants

The Study Information leaflet will be made available to the participant and/or parent/legal guardian for an appropriate amount of time (where possible this will a minimum of 24 hours) prior to consent being obtained. A video presentation of the Study Information leaflet may be screened to an audience, or made available for them to access it remotely. However, participants will have the opportunity to individually question an appropriately trained and delegated researcher before signing consent.

The following general principles will be emphasised:

- Participation in the study is entirely voluntary
- Refusal to participate involves no penalty or loss of medical benefits
- The volunteer may withdraw from the study at any time.
- The volunteer is free to ask questions at any time to allow him or her to understand the purpose of the study and the procedures involved
- The study involves research of an investigational vaccine
- There is no direct benefit to the volunteer from participating
- The volunteer's GP will be contacted to corroborate their medical history (Groups 1, 2 , 7 and 8 only, except group 12 where GPs can be replaced by their HIV consultant). Written or verbal information regarding the volunteer's medical history will be sought from the GP or other sources. This can either be via the study team accessing patient's electronic care summaries from local systems, by contacting the GP practice, or volunteers bringing their medical care summaries from the GP to the study clinicians. However, volunteers in all remaining groups may be enrolled based on medical information obtained during screening and/or enrolment visit, at the physician's discretion.

- Blood samples taken as part of the study may be sent outside of the UK and Europe to laboratories in collaboration with the University of Oxford. These will be de-identified. Volunteers will be asked if they consent to indefinite storage of any leftover samples for use in other ethically approved research, this will be optional.

Participants will be allowed as much time as wish to consider the information, and the opportunity to question the Investigator, their GP or other independent parties to decide whether they will participate in the study. Written informed consent will then be obtained by means of the adult participant or the parent/legal guardian of the participant dated signature, and dated signature of the person who presented and obtained the Informed consent. The person who obtained the consent must be suitably qualified and experienced, and have been authorised to do so by the Chief/Principal Investigator and listed on the delegation log. A copy of the signed informed consent will be given to the participant. The original signed form will be retained at the research study site, in the case report form (CRF).

Updated information that require volunteers to be re-consented will be sent to participants and written re-consent requested at the earliest scheduled visit. If the earliest visit to occur is in the symptomatic pathway, the participant may consent using an electronic signature for infection control purposes. Where appropriate, and when re-consenting in person is not possible (e.g. participants in self-isolation), volunteers may be contacted over the phone and an appropriately trained and delegated researcher will obtain re-consent. In this instance the re-consent discussion will be documented by the researcher, the participant will sign the form (electronic or paper) and a copy will be signed by the researcher. The dates of signature may be different and a fully signed copy will be provided to the participant at the next scheduled visit. The participant may re-consent using an electronic signature.

### **6.3 Inclusion and exclusion criteria**

This study will be conducted in adults who meet the following inclusion and exclusion criteria:

#### **6.3.1 Inclusion Criteria**

The volunteer must satisfy all the following criteria to be eligible for the study:

- Adults aged 18 - 55 years (groups 4, 5, 6 and 11)
- Adults aged 56-69 years (groups 1, 7, and 9)

- Adults aged 70 years and older (groups 2, 8, and 10)
- Able and willing (in the Investigator's opinion) to comply with all study requirements.
- Willing to allow the investigators to discuss the volunteer's medical history with their General Practitioner and access all medical records when relevant to study procedures.
- For females of childbearing potential only, willingness to practice continuous effective contraception (see below) during the study and a negative pregnancy test on the day(s) of screening and vaccination.
- Agreement to refrain from blood donation during the course of the study.
- Provide written informed consent.

Additional Inclusion criteria to Group 12 (HIV sub-study):

- HIV positive
- Receiving antiretroviral therapy
- Undetectable HIV viral load
- CD4>350 cells/mL

### **6.3.2 Exclusion Criteria**

The volunteer may not enter the study if any of the following apply:

- Participation in COVID-19 prophylactic drug trials for the duration of the study.

Note: Participation in COVID-19 treatment trials is allowed in the event of hospitalisation due to COVID-19. The COV002 study team should be informed as soon as possible.

- Participation in SARS-CoV-2 serological surveys where participants are informed of their serostatus for the duration of the study.

Note: Disclosure of serostatus post enrolment may accidentally unblind participants to group allocation. Participation in COV002 can only be allowed if volunteers are kept blinded to their serology results from local/national serological surveys

- Receipt of any vaccine (licensed or investigational) other than the study intervention within 30 days before and after each study vaccination, with the exception of the licensed seasonal

influenza vaccination and the licensed pneumococcal vaccination. Participants will be encouraged to receive these vaccinations at least 7 days before or after their study vaccine.

- Prior or planned receipt of an investigational or licensed vaccine or product likely to impact on interpretation of the trial data (e.g. Adenovirus vectored vaccines, any coronavirus vaccines). This exclusion criteria will not apply to group 11, as recruitment will be targeted at those volunteers who previously received a ChAdOx1 vectored vaccine.
- Administration of immunoglobulins and/or any blood products within the three months preceding the planned administration of the vaccine candidate.
- Any confirmed or suspected immunosuppressive or immunodeficient state (except group 12, where HIV infected participants are allowed); asplenia; recurrent severe infections and use of immunosuppressant medication within the past 6 months, except topical steroids or short-term oral steroids (course lasting  $\leq 14$  days)
- History of allergic disease or reactions likely to be exacerbated by any component of ChAdOx1 nCoV-19 or MenACWY
- Any history of angioedema.
- Any history of anaphylaxis.
- Pregnancy, lactation or willingness/intention to become pregnant during the study.
- Current diagnosis of or treatment for cancer (except basal cell carcinoma of the skin and cervical carcinoma in situ).
- History of serious psychiatric condition likely to affect participation in the study.
- Bleeding disorder (e.g. factor deficiency, coagulopathy or platelet disorder), or prior history of significant bleeding or bruising following IM injections or venepuncture.
- Continuous use of anticoagulants, such as coumarins and related anticoagulants (i.e. warfarin) or novel oral anticoagulants (i.e. apixaban, rivaroxaban, dabigatran and edoxaban)
- Suspected or known current alcohol or drug dependency.
- Any other significant disease, disorder or finding which may significantly increase the risk to the volunteer because of participation in the study, affect the ability of the volunteer to participate in the study or impair interpretation of the study data.
- Severe and/or uncontrolled cardiovascular disease, respiratory disease, gastrointestinal disease, liver disease, renal disease, endocrine disorder and neurological illness (mild/moderate well controlled comorbidities are allowed)

- History of laboratory confirmed COVID-19 (except groups 5d, 5e, 5f, 9, 10 and 11).
  - Seropositivity to SARS-CoV-2 before enrolment (except groups 5d, 5e, 5f, 9, 10 and 11)
  - NB: volunteers with previous NAAT positive results are also allowed in groups 9, 10 and 11

#### Additional Exclusion criteria to Groups 4, 6, 9 and 10

- History of allergic disease or reactions likely to be exacerbated by Paracetamol
  - Note: Caution should be taken when recommending paracetamol to adults who already take paracetamol chronically

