**Group 11: Adults aged 18-55 who previously received a ChAdOx1 vectored vaccine (n=up to 60)**

a1) Two dose ChAdOx1 nCoV-19 0.5mL ( $3.5 - 6.5 \times 10^{10}$  vp, Abs 260, corrected for PS80)\*, (4-6 weeks apart) N=up to 60

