|  | To compare immunogenicity of ChAdOx1 nCoV-19 in participants receiving 1 or 2 doses in groups 1, 2, 7 and 8                           | 
a) Differences in antibody titres (ELISA and Neutralising antibodies) in participants who received 1 or 2 doses of ChAdOx1 nCoV-19 (groups 1, 2, 7 and 8)
 
b) Longevity of immune responses in participants who received 1 or 2 doses of ChAdOx1 nCoV-19
                                                    |
|  | To describe the impact of previous vaccination with other ChAdOx1 vectored vaccines on safety and immune responses to ChAdOx1 nCoV-19 | Differences reactogenicity profile, antibody titres and T-cell responses between groups 5d and 11 and their relationship with anti-vector neutralising antibody titres.                                                                                                                                                  |
|  | To assess the cell-mediated and humoral immunogenicity profile of ChAdOx1 nCoV-19 vaccine in HIV infected adults                      | 
Cell-mediated and humoral responses against SARS-Cov-2 These will be measured by the following:
 
a) Proportion of seroconversion to antibodies (Ab) against SARS-CoV-2 spike protein measured by ELISA.
 
b) Interferon-gamma enzyme linked immunospot (ELISpot) responses to SARS-CoV-2 spike protein
 |

|  |                                                                                                                        |                                                                                                                                                                                                                                                                                                                                                                                   |
|--|------------------------------------------------------------------------------------------------------------------------|-----------------------------------------------------------------------------------------------------------------------------------------------------------------------------------------------------------------------------------------------------------------------------------------------------------------------------------------------------------------------------------|

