### **3.3 Previous clinical experience**

ChAdOx1 vectored vaccines expressing different inserts have previously been used in over 320 healthy volunteers taking part in clinical trials conducted by or in partnership with the University of Oxford in the UK and overseas (table 1 and 2). Most importantly, a ChAdOx1 vectored vaccine expressing the full-length Spike protein from another Betacoronavirus, MERS-CoV, has been given to 31 participants to date as part of MERS001 and MERS002 trials. ChAdOx1 MERS was given at doses ranging from  $5 \times 10^9$  vp to  $5 \times 10^{10}$  vp (table 2) with no serious adverse reactions reported. Further safety and immunogenicity results on ChAdOx1 MERS can be found on the Investigator's Brochure for ChAdOx1 nCoV-19 for reference.

Clinical trials of ChAdOx1 vectored vaccines encoding antigens for Influenza (fusion protein NP+M1), Tuberculosis (85A), Prostate Cancer (5T4), Malaria (LS2), Chikungunya (structural

polyprotein), Zika (prM and E), MERS-CoV (full-length Spike protein) and Meningitis B are listed below.

None of the below mentioned clinical trials reported serious adverse events associated with the administration of ChAdOx1, which was shown to have a good safety profile.

CONFIDENTIAL

Table 1. Clinical experience with ChAdOx1 viral vector vaccines.

| Country            | Trial  | Vaccine                 | Age                     | Route | Dose                    | Number of
Volunteers (Received
ChAdOx1) | Publication / Registration Number                                                     |
|--------------------|--------|-------------------------|-------------------------|-------|-------------------------|-----------------------------------------------|---------------------------------------------------------------------------------------|
| UK                 | FLU004 | ChAdOx1 NP+M1           | 18-50                   | IM    | 5x10  vp    | 3                                             | Antrobus et al, 2014. Molecular Therapy.
DOI: 10.1038/mt.2013.284
 |
|                    |        |                         |                         |       | 5x10  vp    | 3                                             |                                                                                       |

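### The group 11 waiver lifts the coronavirus-vaccine exclusion along with the adenovirus-vector exclusion, so spike priming could enter group 11 but not its comparator 5d

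*Protocol*

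**What the plan says.** Section 6.3.2 of the Protocol excludes volunteers with "Prior or planned receipt of an investigational or licensed vaccine or product likely to impact on interpretation of the trial data" and gives as examples "e.g. Adenovirus vectored vaccines, any coronavirus vaccines". It then adds: "This exclusion criteria will not apply to group 11, as recruitment will be targeted at those volunteers who previously received a ChAdOx1 vectored vaccine". The waiver carries no limit by vaccine insert.

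The Synopsis and section 5.1 define group 11 as up to 60 adults aged 18 to 55 who have had an earlier ChAdOx1-vectored vaccine. Its tertiary objective is "To describe the impact of previous vaccination with other ChAdOx1 vectored vaccines on safety and immune responses to ChAdOx1 nCoV-19". The outcome is the difference in reactogenicity, antibody titres and T-cell responses "between groups 5d and 11 and their relationship with anti-vector neutralising antibody titres". Section 4 repeats the objective for immune responses and keeps the word for vaccines other than the study vaccine.

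Section 3.3 includes among the earlier ChAdOx1 vaccines "a ChAdOx1 vectored vaccine expressing the full-length Spike protein from another Betacoronavirus, MERS-CoV". Section 3.4.2 says that COV001 gave ChAdOx1 nCoV-19 or MenACWY to UK adults aged 18 to 55.

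**The concern.** The reason given for the waiver is that group 11 recruits people who have had a ChAdOx1 vector before. That justifies lifting the adenovirus-vector part of the exclusion and nothing more. The coronavirus-vaccine part guards a separate matter, namely prior exposure to a spike antigen, and spike response is the readout of this comparison.

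With both parts lifted, group 11 can contain people with vector exposure alone and people with vector plus spike exposure. The question behind the group is whether earlier vector exposure alters the response, presumably by lowering it. Spike priming, if present, would push the other way. A blunting effect could then look smaller than it is.

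The planned relationship with anti-vector titre is exposed for the same reason. Spike exposure delivered on the same vector is tied to the anti-vector titre, so adjusting for titre alone could not separate the two effects in those people.

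**Working it through.** **Step 1: does another criterion close the gap?** There is no sample-size or power figure behind group 11 to reproduce, so the first check is of the text.

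| Protocol rule | Group 11 | Group 5d |
|---|---|---|
| Prior adenovirus-vectored vaccine (6.3.2) | allowed | excluded |
| Prior coronavirus vaccine (6.3.2) | allowed | excluded |
| COVID-19 history or seropositivity (6.3.2) | allowed | allowed |
| Screening SARS-CoV-2 serology (7.2) | not done | not done |
| 30-day rule on other vaccines (6.3.2) | spacing only | spacing only |
| Group definition (Synopsis, 5.1) | earlier ChAdOx1 vaccine, any insert | no vaccine-history element |

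Nothing specifically bars a recipient of a coronavirus-insert ChAdOx1 vaccine from group 11. Infection-derived priming can occur in either group; vaccine-derived spike exposure is admitted only in group 11.

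**Step 2: which histories can enter?** A ChAdOx1 MERS recipient meets both the group definition and the objective's wording. A ChAdOx1 nCoV-19 recipient from COV001 meets the group definition but not the objective, because the limit to other ChAdOx1 vaccines appears in no eligibility criterion.

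**Step 3: scale, for illustration only.** The counts come from Tables 1 and 2 in section 3.3.

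- UK non-cancer, non-MERS recipients: FLU004 15 + FLU005 69 + TB034 42 + VAC067 13 + VAMBOX 29 + CHIK001 24 + ZIKA001 9 = 201.
- UK MERS recipients: 6 + 9 + 9 = 24. Section 3.3 gives 31 MERS recipients in all, and 6 + 9 + 9 + 4 + 3 = 31, so the three prime-boost participants are already counted within the 24.
- Share if recruitment follows the pool: s = 24 / (201 + 24) = 24/225 = 10.7%; 60 × 0.107 = 6.4, or about 6 people.
- Cross-check on the overall totals in section 3.3: 31/320 = 9.7%; 60 × 0.097 = 5.8, again about 6.
- Leaving out the 24 people in the FLU005 arms aged over 50: 24 / (177 + 24) = 11.9%; 60 × 0.119 = 7.1, or about 7 people.

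If a share s of the group responds f-fold higher and the rest are unaffected, the mean log response rises by s × log f. The geometric mean is therefore multiplied by f^s, which would hide a true reduction of 1 − 1/f^s. With s = 24/225:

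| Assumed priming f | Inflation f^s | Reduction hidden |
|---|---|---|
| 1.5-fold | 1.5^0.107 = 1.04 | 4% |
| 10-fold | 10^0.107 = 1.28 | 22% |

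The Protocol gives no priming figure, so f is an assumption throughout, and so is recruitment in proportion to the pool.

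**The case against.** The case for leaving the text alone has real strength.

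- **The objective shows the intent.** It concerns other ChAdOx1 vaccines, so prior ChAdOx1 nCoV-19 recipients were not meant to enter, and nothing suggests that COV001 vaccinees were sought. This stands as to intent. For them the fault is a mismatch between the eligibility text and the objective. A reader might infer a large inflow from COV001, but section 3.4.2 gives only the total enrolled, without the split between vaccines, so no number can be put on it.
- **MERS recipients fit the objective.** This also stands: ChAdOx1 MERS is another ChAdOx1 vaccine, and admitting it contradicts nothing. Nor does the Protocol say that MERS spike primes the response to SARS-CoV-2 spike. Section 3.1 places MERS-CoV in lineage C with 50% shared sequence, against more than 79% for SARS-CoV, and SARS-CoV-2 in lineage B. Priming from MERS is a possibility, and the effect could be close to nil.
- **Spike-naivety was never required.** Groups 5d and 11 both accept prior infection, and both have a day 0 immunology sample (Tables 5 and 12), so baseline response could be taken into account, perhaps in the SAP. That softens the point. It does not remove the imbalance, because vaccine-derived spike exposure is confined to group 11.
- **Investigators keep discretion.** Section 6.3.2 also excludes diseases, disorders or findings that impair interpretation, and bars COVID-19 prophylactic drug trials, which might be read to cover COV001. Neither is a dependable substitute for a vaccine criterion that has been expressly waived.

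A reader might also infer from section 6.3.1, which lists group 11 only under "Adults aged 18 - 55 years (groups 4, 5, 6 and 11", that prior ChAdOx1 exposure is not required. The Synopsis and section 5.1 do require it. For the same reason, a recipient of some other COVID-19 vaccine would not qualify on that history alone.

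**Conclusion.** The point holds as a minor one. The waiver is broader than its stated reason. It lets coronavirus-insert ChAdOx1 recipients into group 11 while group 5d excludes them, and so leaves the group's one planned comparison, and its link to anti-vector titre, open to a mixture of vector immunity and spike priming.

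The size cannot be fixed from the Protocol. The illustrative range of 1.04- to 1.28-fold rests on proportional recruitment from the listed UK pool and on assumed priming of 1.5- to 10-fold in MERS recipients. It leaves out any ChAdOx1 nCoV-19 recipients, whose number is unknown.

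The Protocol does not support extending this to the trial's main conclusions. The objective is tertiary and descriptive, the group is open-label and non-randomised with at most 60 people, and neither the primary efficacy analysis nor the serious adverse event endpoint is shown to be affected.

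**What to change.** In section 6.3.2, limit the group 11 waiver to prior ChAdOx1-vectored vaccines that do not encode a coronavirus antigen, and state that the exclusion of coronavirus vaccines still applies to group 11.

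Group 11 was added in version 9.0 and section 7.6.1 refers to a completed primary efficacy analysis, so enrolment may well be finished. In that case the change belongs in the analysis: record which ChAdOx1 vaccine each group 11 participant had, report recipients of a coronavirus insert separately, and run the 5d versus 11 comparison and the anti-vector relationship without them.

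The cost is one sentence in the Protocol, or one split by prior vaccine, and a slightly smaller group 11 analysis set: about 6 of 60 under the illustration above.
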